## Abstract

Physical activity is beneficial for improving health and reducing sick leave absences. This article describes a protocol for an intervention using an interactive accelerometer smartphone application, telephone counselling, and physical activity recordings to increase the physical activity of workers in the military and improve their health. Under the protocol, employees from six military brigades in Finland will be randomly assigned to intervention and control groups. The intervention group’s participants will use accelerometers to measure their daily physical activities and their quality of sleep for six months. They will receive feedback based on these measurements via a smartphone application. The intervention group’s participants will be encouraged to exercise for two hours per week during working hours, and to participate in telephone counselling. The control group’s participants will continue with their normal exercise routines, without the accelerometer or feedback. The participants of both groups will be measured at the baseline, after the intervention period, and six months after the end of the intervention. The measurements will include accelerometer recordings, biochemical laboratory tests, body composition measurements, physical fitness tests, and questionnaires on sociodemographic factors, physical activities, and health. The primary outcomes will indicate changes in physical activity, physical fitness, and sick leave absences. The findings will help to develop a straightforward and cost-effective model for supporting the health and working capabilities of employees in the military and other workplaces.

## 1. Introduction

Physical activity has many health benefits. It reduces the risk of cardiovascular diseases such as strokes, dyslipidemia, and atherosclerosis. It also reduces insulin resistance and prevents the development of type 2 diabetes. Physical activity also has positive effects on sleep and mental health [1,2]. Obesity increases the risk of type 2 diabetes, coronary disease, high blood pressure, and nonalcoholic fatty liver disease [3]. Visceral fat is a particular health risk [4]. Regular long-term endurance training boosts cellular aerobic energy production and accelerates the oxidation of lipids around the body [5], leading toa reductions in body fat, waist circumference [6], and harmful visceral fat tissue. Physically active members of the working population also have fewer sick leave absences than those individuals who are in poor physical condition [7,8].

Based on surveys and accelerometer measurements carried out among the working population in Finland, the volume of endurance training is not sufficient to sustain the health and physical fitness of the population. Objective data recorded by accelerometers show that 76% of the day is passive time, spent mostly sitting [9]. The poor physical fitness of workers leads to noticeable costs for employers, as well as reduced performance, eliciting the need for physical activation measures.

The trend towards reduced physical activity levels is seen in the military environment, even though soldiers’ good physical performance is essential for success in operations. Therefore, working armies, such as those in the Finnish Defence Forces (the FDF), set special demands for physical fitness. According to law, professional soldiers in the FDF must maintain good physical fitness to meet the demands of their work. For civilian workers in the FDF, maintaining good physical fitness is optional, but the employer can require good physical performance in demanding tasks and peacekeeping operations [10]. A wide survey done [11] among employees of the FDF revealed insufficient exercise habits, with only 51% of the employees in the FDF exercising three times a week.

Reduced physical activity levels increase the risk of metabolic diseases, cardiovascular diseases, and other diseases [1], resulting in increased human resources costs. In the military workplace, Kyröläinen et al. [12] reported that poor muscle fitness and endurance, as well as a high body mass index (BMI), are risk factors for productivity loss, causing additional costs for employers. In 2016, the FDF estimated that sick leave absences cost 35 million euros [13].

To maintain the required physical performance of its workers, the FDF has developed a set of guidelines. To activate workers, one measure in the guidelines is to offer the opportunity to exercise during work for two hours per week, if annual fitness tests are performed [10]. Positive results have previously been achieved using physical training during the workday, showing that these FDF guideline measurements are a step in the right direction [8,14,15,16].

A limited number of studies have been published concerning physical activity and its effects on health in military populations. Additional actions are needed to promote the health and exercise habits of military workers. The present study aims to develop an intervention protocol to increase the physical activity of workers in military settings. Promising results have previously been demonstrated in interventions using accelerometers with online feedback and smartphone techniques in adolescents and adult civilians [17,18,19,20]. In the present study, the use of an interactive accelerometer with a smartphone application, telephone counselling, and the possibility of exercising for two hours a week during working hours to increase participants’ daily activities has been developed. The objectives of this study are to improve health outcomes, reduce stress, improve the quality of sleep, and improve the work performance of employees. The study also investigates whether increased physical activity during the intervention will improve physical fitness and lead to reduced sick leave absences. Thus, the hypothesis of the present study is that the intervention will result in increased daily physical activity, improved physical fitness, health promotion, and reduce sick leave absences. Comparing the changes in the measured parameters between the intervention and control groups will enable the effects of the intervention to be assessed.

## 2. Methods/Design

### 2.1. Participants

The participants will be recruited from six brigades in Finland. Information about the study will first be delivered in an online presentation via the intranet. Later, real-life presentations and written information will be provided to participants. Each civilian and military worker in the FDF, aged between 19–60 years, can be accepted for participation in the study, subject to health considerations including fitness tests and regular occupational health care examinations. Exclusions based on health will be determined following an occupational physician’s examination. Voluntary participants who meet the inclusion criteria will be asked to give their written consent before taking part in the baseline measurements.

### 2.2. Randomization

The study’s participants will be asked to complete a randomization questionnaire. To maximize participation, two-thirds of will be assigned to an intervention group and one-third to a control group (Figure 1). The questionnaire will ask participants to provide personal information to establish homogenous groups according to age, sex, working status (civilian worker vs. soldier), and physical activity. The type of smartphone or other smart device in use will be determined via the questionnaire. Our assumption is that the type of smartphone will not create bias in the results, and this assumption will be confirmed when the results are analyzed. Participants in the intervention group will be asked to confirm that they have a device that supports the application used in the research setting.

### 2.3. Power Calculation and Sample Size

Before the intervention begins, power calculations will be determined, based on the means and standard deviations of personal fitness indices and short sick leave absences (i.e., seven or fewer calendar days) of FDF personnel. According to the results of an endurance test and a muscle strength test, participants’ endurance and muscle strength indices will be determined, using age-dependent reference values. The fitness index will be calculated as an average of the endurance and muscle strength indices [10]. The calculations will be based on the assumption that sick leave absences would reduce as fitness indices increase by a certain amount, i.e., that sick leave absences will reduce by 0.35 days per year for professional soldiers and by 0.40 days per year for civilian workers. The fitness indices will be assumed to increase by 0.14 for male soldiers; 0.45 for female soldiers; 0.34 for male civilian workers; and 0.24 for female civilian workers. For the evaluation of physical fitness, an appropriate number of study participants is approximately 175 soldiers and 99 civilians. To evaluate sick leave absences, an appropriate number of participants is approximately 115 soldiers and 97 civilians (G*Power 3.1.9.2, Wilcoxon signed-rank test (matched pairs), correlation between groups assumption r = 0.80).

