### 3.6. Statistical Analysis

The continuous distributions will be described using means with standard deviations; regarding categorical data, the number of cases with percentages will be used. Differences between the intervention group and the control group will be tested using an independent samples *t*-test, a Pearson Chi-Square test, or a Fisher’s Exact test. Regression analyses will be used to evaluate the role of physical activity in the changes to physical fitness and the number of sick leave days. Changes in physical fitness and the number of days of sick leave, according to follow-up times and for comparison of the study groups, will be analyzed using general/generalized linear models (univariate, multivariate, and repeated measures) and regression analyses. The drop-out rate can be determined by comparing the number of participants attending baseline measurements to the number of participants attending follow-up measurements. Intention-to-treat analysis will be used to compare changes induced by the implemented intervention of the treatment groups, including all participants as originally allocated after randomization. In addition, a per-protocol analysis will be used to compare changes in the intervention participants who completed the treatment originally allocated. P-values under 0.05 are considered statistically significant. IBM SPSS Statistics version 26.0 for Windows (SPSS Inc., Chicago, IL, USA) was used for statistical analyses.

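### The sample sizes in section 2.3 come from a matched-pairs test, whereas the trial compares changes between two independent arms randomised 2:1

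*Protocol article*

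**What the plan says.** Section 2.3 bases its calculation on personnel data ("based on the means and standard deviations of personal fitness indices and short sick leave absences"). The assumed effects are written as changes, not as differences between arms. For sick leave: "sick leave absences will reduce by 0.35 days per year for professional soldiers and by 0.40 days per year for civilian workers". For fitness: "The fitness indices will be assumed to increase by 0.14 for male soldiers; 0.45 for female soldiers; 0.34 for male civilian workers", with 0.24 for female civilian workers. The resulting numbers are 175 soldiers and 99 civilians for fitness, and 115 soldiers and 97 civilians for sick leave. The method is given as "G*Power 3.1.9.2, Wilcoxon signed-rank test (matched pairs), correlation between groups assumption r = 0.80".

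The rest of the article describes a two-arm comparison:

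- Section 1: "Comparing the changes in the measured parameters between the intervention and control groups will enable the effects of the intervention to be assessed".
- Section 2.2: "two-thirds of will be assigned to an intervention group and one-third to a control group".
- Section 3.6: "Differences between the intervention group and the control group will be tested using an independent samples" t-test. It also plans linear models comparing the study groups, and an intention-to-treat comparison of the groups as randomised.

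No section pairs individual participants across the arms, and none gives a sample size for the between-arm comparison.

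**The concern.** A matched-pairs test on N people carries one source of error, the spread of the paired differences. A comparison of changes between two arms also carries the sampling error of the control arm, and the 2:1 split leaves that arm with only a third of the participants. A number that is adequate for the first is well short for the second.

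Fitness and sick leave are both primary outcomes, and the hypothesis is about the effect of the intervention. As it stands, the only sample-size justification in the article supports a statement about change over time and not about intervention against control. If the stated numbers were the numbers analysed, a non-significant difference between the arms could say little.

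**Working it through.** **Inputs.** From section 2.3: N = 175, 99, 115, 97; r = 0.80; sick-leave effects 0.35 and 0.40 days per year. From section 2.2: 2:1 allocation. From section 3.6: the 0.05 threshold, stated for the analysis and assumed here for the sizing. Not printed: SD, target power, sidedness. I take power of 80, 90 and 95%, two-sided unless noted.

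**1. The plan's own figures.** They cannot be reproduced without the SD and target power. What can be done is to find the standardised paired change each N implies, dz = (z_α + z_β)/√N. For 80% power, 2.80/√N gives 0.212, 0.282, 0.261 and 0.284 for N = 175, 99, 115 and 97. The noncentral t with Wilcoxon efficiency 3/π gives 0.218, 0.291, 0.270 and 0.294.

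**2. Variance ratio.** Let s be the SD of the within-person change.

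- Paired, one group: s²/N.
- Two arms of 2N/3 and N/3, change scores: s²(3/(2N) + 3/N) = 4.5 s²/N.
- With baseline adjustment: s² = 2(1 − 0.80)SD² = 0.40 SD² is replaced by (1 − 0.80²)SD² = 0.36 SD². The factor becomes 4.5 × 0.36/0.40 = 4.05.

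The factor 4.5 needs no SD, alpha or target power. The factor 4.05 needs only r.

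**3. Detectable difference at the same N.** √4.5 = 2.12 and √4.05 = 2.01. For sick leave, 0.35 days becomes 0.70 to 0.74, and 0.40 days becomes 0.80 to 0.85.

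**4. Power at each stated N.** Power = Φ((z_α + z_β)/√f − 1.96), with f = 4.5 or 4.05 and z_α + z_β = 2.80, 3.24 or 3.605. For example, Φ(2.80/2.12 − 1.96) = Φ(−0.64) = 0.26. The result is the same for all four N, because each was sized to the same target.

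**5. Pooling.** If k strata were each sized to the target, and are combined so that their squared noncentralities add (the most favourable weighting), the noncentrality is multiplied by √k. Soldiers and civilians give k = 2. For fitness there are four sex-by-status effects but two N. If the N are sums of four separate calculations, k = 4.

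| Power in % if the paired target was | 80 | 90 | 95 |
|---|---|---|---|
| Per stated N, change score | 26.1 | 33.3 | 39.7 |
| Per stated N, baseline-adjusted | 28.5 | 36.3 | 43.3 |
| Pooled, k = 2, change score | 46.3 | 58.0 | 67.1 |
| Pooled, k = 2, baseline-adjusted | 50.4 | 62.5 | 71.7 |
| Fitness only, k = 4, change score | 75.2 | 86.3 | 92.5 |
| Fitness only, k = 4, baseline-adjusted | 79.5 | 89.6 | 94.8 |

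**6. Variants.**

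- One-sided 0.05, per stated N, change score: about 32/40/46%.
- A t-test credited with π/3 over the Wilcoxon: about 27/35/41%.
- Stated N read as the intervention arm only, with N/2 controls added: variance s²(1/N + 2/N) = 3s²/N, and power of about 37/46/55%.

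All figures assume that controls do not change, that both arms have the same SD, and that nobody drops out. Section 2.4.2 lets controls exercise in working hours, so any improvement there would lower power further.

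**The case against.** The mismatch of test and design is hard to dispute, but much can be said against its size.

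**The fitness numbers allow a milder reading.** Four effects and only two N are printed. If the N were summed over four calculations, a pooled analysis comes close to target. This stands, and the range for fitness must include it. It does not help sick leave, which has two effects and two N.

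**Section 3.1 frames several primary changes as before against after, without naming the arms.** That is so, but sections 1 and 3.6 state plainly that the intervention effect rests on comparing the groups.

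**The pre-post reading is an inference.** Section 2.3 says only matched pairs. Still, no pairing across arms is described, a 2:1 split cannot be fully paired one to one, and section 3.6 treats the arms as independent.

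Several stronger readings are tempting, and the documents do not support them:

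- *The printed N are miscalculated.* Without the SD and target power, no printed figure can be shown to be wrong for the test named.
- *The trial is underpowered.* The N are approximate and are not stated as enrolment. The participant flow is in Figure 1, which is not shown.
- *The correlation of 0.80 is a second error, because independent arms do not correlate.* On the pre-post reading it is a within-person correlation, and only its label is awkward.
- *The 0.14 index points become about 0.30.* The 0.14 applies to male soldiers, while 175 covers all soldiers.
- *Analysts would drift to within-arm p-values.* Section 3.6 commits to an intention-to-treat comparison of the groups.

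**Conclusion.** The point holds. The numbers in section 2.3 are justified for a paired comparison and not for the 2:1 between-arm comparison that the article sets out to make. The firm part is the variance factor: 4.5, or about 4.05 with baseline adjustment at r = 0.80.

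The power figures are conditional on an unstated target and on the assumptions listed above. For sick leave the shortfall is large both within each group and pooled. For fitness it is large within each stated N, but on pooling it runs from large to almost none, depending on how 175 and 99 were built up.

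**What to change.** Replace the calculation in section 2.3 with a two-group, 2:1 calculation on the baseline-adjusted difference between arms, pooled over soldiers and civilians with working status as a covariate.

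- State the SD, alpha, sidedness and power.
- Say whether the fitness numbers are sums over sex.
- Name the time point that is sized. By Table 1, controls have fitness tests only at baseline and six months after the end of the intervention, so a between-arm fitness comparison directly after the intervention is not available.
- Report the power or the detectable difference at 175/99 and 115/97, in place of the statement that these numbers are suitable, which does not hold for showing the intervention effect.

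The cost is one rewritten paragraph and a new run of the power program. No extra enrolment is needed and the planned analysis does not change. The only downside is that the stated power will look less favourable.

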### 2.4. Intervention

The intervention will use a technique involving an interactive accelerometer, smartphone application, telephone counselling, and daily physical activity recordings. The intervention will last six months, and measurements of the intervention participants will be performed at the baseline, immediately after the intervention, and six months after the intervention. The intervention procedure is described in Table 1.

#### 2.4.1. Intervention Group

##### Accelerometer Measurements during the Intervention and Smartphone Application Feedback

For six months, the intervention group will wear an interactive accelerometer (Movesense, Suunto, Finland) and receive information on their daily physical activities and quality of sleep via a smartphone application (ExSed, UKK, Terveyspalvelut Oy, Tampere, Finland) The accelerometer will be downloaded with ExSed algorithms, with a mean amplitude deviation MAD and angle for posture estimation APE that have been developed in the UKK Institute (Tampere, Finland). The MAD-APE algorithms can differentiate reliably between sitting and standing [21,22,23]. The accelerometers will be worn on participants’ hips during waking hours and on their wrists during sleep. The accelerometer will transmit the collected physical activity information and sleep data to the ExSed application via Bluetooth. The ExSed application will provide constant feedback on users’ physical activities (e.g., light and moderate activity, steps), sedentary time (e.g., sitting, standing), and quality of sleep (total sleep time, restless sleep time, restful sleep time). The recorded data will be saved to a cloud service [24].

##### Telephone Counselling

The intervention group participants will receive telephone counselling on one occasion during the six-month intervention, providing feedback about their exercise habits. During the counselling session, which will last 10 min, participants will be interviewed about the progression in their exercise habits and hindering factors. The counsellor will guide the participants in finding solutions to existing problems. The telephone counselling sessions will be carried out by two physical education instructors and a research physician, using a pre-planned interview sheet.

##### Training Diary

The intervention group’s participants will be encouraged to exercise two hours per week during working hours, a benefit that is offered to employees under existing FDF guidelines. A training diary will be used to assess these workouts and to differentiate them from the collected accelerometer data. Participants will note in their diaries when they have exercised during working hours (Excel worksheet). The duration and mode of the exercises will be reported.

#### 2.4.2. Control Group

The control group’s participants will continue their normal exercise routines after the baseline measurements, without an accelerometer or feedback. They can benefit from exercising during working hours, but they will not be specifically encouraged to do so, and no exercise diaries will be required.

### 2.5. Measurements

All participants will be subject to baseline measurements at the beginning of the study, and similar measurements at the end of the study. Following the intervention, the intervention group participants will again be subject to all these measurements to observe the effects of the intervention. The control group participants will be subject to physical activity measurements via an RM42 accelerometer for two weeks, to examine whether any changes in their physical activities have taken place due to participation in the study, even without taking part in the intervention.

#### 2.5.1. The Questionnaire

The study’s participants will be asked to answer a questionnaire with topics concerning their lifestyle habits, stress, physical health, and mental health. The questions have been previously validated in various studies (see below). Participants will be asked to fill in the questionnaire online, accessing it from a link sent to them by e-mail. The lifestyle questions will inquire about usage of tobacco products (e.g., cigarettes and snus), alcohol consumption, eating, sleeping, and physical activity. To survey their dietary habits, participants will be also asked about their consumption of different food products during the previous week [25]. The sleep questions will be concerned with the duration of sleeping time, quality of sleep, and interruptions of sleep, as set out in the Nordic Sleep Questionnaire [26]. The questions about physical activity habits will include questions about the participants’ total physical activity, which will be categorized into leisure-time physical activities (LTPA), commuting activities (CPA), and occupational physical activities (OPA) [27]. In addition, inactivity (e.g., screen time), self-reported illnesses, uses of medication, experiences of stress, moods, and motivational factors related to physical activity, education, and working status will be studied [28].

